**6*, 12 and 24 months follow up**	
Work	Return to work, modified duties, hours
Social life	Satisfaction with social relationships
Health related quality of life	Likert scale for overall health, Global Perceived Effect (GPE) [25], EQ5D3L [23] and SF12 [24].
Compensation	Claim made, claim type, claim acceptance, fault/blame, legal representation, disputes, medico-legal assessments, claims costs, satisfaction with claims process, previous claim history.
Disability and functioning	History of any disability, World Health Organisation Disability Assessment Schedule II (WHODAS II) [28].
Psychological factors	Depression, Anxiety and Stress Scale (DASS21) [29] and Impact of Events Scale (IES-R) [30], expectation to recover using OMPQ.
Pain	Numeric rating scale (NRS) [26]

*In addition circumstances of crash will also recorded as open verbatim at 6 months.

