### Objectives

The specific objectives of the study in context of the New South Wales, compulsory third party scheme are as follows:

1. To determine whether particular prognostic factors, including those related to health, socio-demographic and economic status, are predictors of outcome following injury.

2. To determine whether particular factors linked to compensation are predictors of outcome.

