**Baseline**	
Socio-demographic	Age, sex, place of birth, primary language, education, marital status
Employment	Employment status, occupation, income
Health	BMI ( height and weight), history of chronic illness
Health related quality of life	Likert scale for overall health, EQ5D3L [23] and SF12 [24] prior to crash and at baseline, Global Perceived Effect (GPE) [25].
Lifestyle habits	Smoking status and alcohol consumption
Pain	Numeric Rating Scale (NRS) [26], Pain Catastrophising Scale (PCS) [27], Orebro Musculoskeletal Pain Question (OMPQ, short form) [27].
Disability and functioning	History of any disability, World Health Organisation Disability Assessment Schedule II (12-item version) (WHODAS II) [28].
Psychological factors	Perceived threat to life and disability, Depression, Anxiety and Stress Scale (DASS21) [29] and Impact of Events Scale (IES-R) [30], expectation to recover using OMPQ.
Health Care Utilisation	Visit to health care professionals 3 months prior to crash, history of health care utilization in 12 months prior to crash through Medicare data linkage
Injury	Type of injury and associated hospitalisation
Crash related factors	Role, perceived danger of death and disability
Work	Return to work, modified duties, hours
Social life	Satisfaction with social relationships

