### Baseline and follow-up data and study endpoints

Data from multiple domains will be recorded at baseline and the follow-up interviews as reported in Table 
2. Standardised instruments are used that assess the relevant domains based on previous research.

The primary outcomes are health related quality of life, disability and functioning at 6, 12 and 24 months after injury in motor vehicle crash. The secondary outcomes are pain status, psychological health, return and modification to work status, social outcomes, role of compensation and health care utilisation.

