### Data analysis

Summary statistics will be used to describe the profile of participants in the study at each time point. Frequencies and percentages, means and standard deviations, and medians and interquartile ranges, will be used to summarise key predictors and outcomes, depending on the distribution of the data collected for these variables. Key participant groups (for example, participants lost to follow-up vs. not lost to follow-up, compensable vs. non-compensable) will be compared using chi-square tests for categorical characteristics, and either independent t-tests or Mann–Whitney U-tests for continuous variables depending on the distributional characteristics of particular variables.

To analyse change in outcome over time, and to explore predictors of outcome, multilevel mixed effects regression models will be fitted with a random effect for patient to allow for excess correlation in outcomes measured repeatedly from the same participant. Mixed effects modelling is warranted due to the longitudinal nature of the study. Logistic regression will be used for binary outcomes and linear regression for continuous outcomes. Univariate and bivariate models will be performed to explore the association between individual predictors and each outcome. To establish whether the rate of change in the outcome differs across participant sub-groups (for example, compensable vs. non-compensable), an interaction term between each variable and follow up time point will be included in the regression model. Interaction terms between various predictors will be examined in order to identify potential effect modification. Multivariate mixed effects models will be used to identify important predictors of outcome, adjusted for potential confounders, and including key a priori interactions. Odds ratios, adjusted odds ratios, and 95% confidence intervals will be reported for logistic models, while coefficients and 95% confidence intervals will be reported for linear models.

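### Compensation factors that change over time are first recorded at the same interviews as the primary outcomes, with no stated time order, so the model as described cannot tell predictor from consequence

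*Protocol article*

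**What the plan says.** The second of the two objectives is "To determine whether particular factors linked to compensation are predictors of outcome".

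The baseline block of Table 2 covers socio-demographic, health, pain, disability, psychological, injury, crash and work items, with quality of life recorded "prior to crash and at baseline". It has no compensation row. The follow-up block, for 6, 12 and 24 months, lists "Claim made, claim type, claim acceptance, fault/blame, legal representation, disputes, medico-legal assessments, claims costs, satisfaction with claims process", together with previous claim history.

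Under Baseline and follow-up data and study endpoints, "The primary outcomes are health related quality of life, disability and functioning at 6, 12 and 24 months after injury in motor vehicle crash". The same paragraph also puts "role of compensation and health care utilisation" among the secondary outcomes.

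The Data analysis section describes mixed models with a random effect for participant and interactions with follow-up time point, and says that "Multivariate mixed effects models will be used to identify important predictors of outcome, adjusted for potential confounders, and including key a priori interactions". It gives no lag or ordering between compensation status and outcome.

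The Discussion hypothesises that people with worse pre-injury health, more pain and lower mood will both fare worse and claim more often. It says the compensation hypothesis will be adjusted for disability, pain, injury severity and claim duration, without saying when these are measured. It hopes the results will inform policy on how compensation factors could improve outcomes.

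**The concern.** Someone doing badly at 6 months has more reason to have claimed, retained a lawyer, entered a dispute, run up costs and be dissatisfied. If the exposure and the outcome come from the same interview, an association between them is compatible with either direction. The article supplies the reverse path itself: it expects poor health to lead to claiming, and it lists the role of compensation as an outcome as well as a predictor.

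One of only two objectives, and the hoped-for policy use, depend on direction. The random effect deals with correlation between repeated measurements, and the time interaction tests whether change differs between groups. Neither orders exposure and outcome in time.

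**Working it through.** No figure in the article is in dispute. The check is of timing, followed by an illustration of size.

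**Timing, from the article**

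| Item | Baseline | 6 months | 12 months | 24 months |
|---|---|---|---|---|
| Health, disability, pain, mood | yes | yes | yes | yes |
| Compensation items | no | yes | yes | yes |

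A 12- or 24-month outcome has an earlier compensation record in Table 2. A 6-month outcome has none.

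**Illustration A: same-visit regression, true effect zero.** All inputs are assumed; none is in the article.
- Standardised health scores, correlated 0.6 from baseline to 6 months and 0.75 per later step.
- Exposure prevalence about 30%.
- Odds of exposure multiplied by 1.25, 1.5 or 2.0 per SD of worse health.
- n = 400,000, ordinary least squares.

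The table gives the size of the false effect in SD, in the direction of worse health among the exposed.

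| What drives the exposure | Model | 1.25 | 1.5 | 2.0 |
|---|---|---|---|---|
| 6-month health | 6-month outcome, adjusted for baseline | 0.14 | 0.25 | 0.42 |
| 6-month health | 12-month outcome, adjusted for baseline only | 0.10 | 0.19 | 0.32 |
| 6-month health | 12-month outcome, adjusted for baseline and 6-month health | 0.00 | 0.00 | 0.00 |
| Baseline health only | 6-month outcome, adjusted for baseline | 0.00 | 0.00 | 0.00 |

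For scale, the difference detectable with 90% power at n = 1,500 and 30% prevalence is (1.960 + 1.282)/√(1,500 × 0.3 × 0.7) = 3.242/17.75 = 0.18 SD.

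**Illustration B: different inputs.** n = 2,400 × 0.70 = 1,680, 400 runs. The correlation is 0.7 from baseline to the time of claiming and 0.8 per later step, and log-odds of exposure are 0.2, 0.5 or 1.0 per SD of worse health. The same-visit false effect, adjusted for baseline, is 0.08, 0.20 and 0.37 SD, with nominal 5% tests significant in 49%, 99.5% and 100% of runs. With the lag and adjustment for baseline and 6-month health, the effect is about 0 and the rates are 4.5%, 5.2% and 3.5%.

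**Illustration C: a model of the kind the article describes.** Random intercept, three visits, exposure that persists once acquired, adjusted for baseline, n = 1,680, odds ratios as in A. The false effect is 0.11, 0.21 and 0.33 SD.

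Lagging alone is therefore not enough (second row of A). Adjustment for the outcome at the earlier visit is what removes this bias.

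**What the lagged model costs.**
- If a true effect of 0.30 SD is fully realised by 6 months, the same-visit model recovers 0.30, while the lagged model adjusted for 6-month health returns 0.00.
- If the health scores have an assumed reliability of 0.7 to 0.8, the lagged model keeps a residual false effect of about 0.03 to 0.12 SD.

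**The case against.** The strongest reply is that the article is silent on lag and does not choose a same-visit regression. It is a condensed report, and a statistical analysis plan that is not shown could set the ordering. The authors plainly have the reverse path in view, since they hypothesise it. They collect health, pain, disability and mood at baseline, link pre-injury Medicare records, and state an adjustment for disability, pain and injury severity. The 6-month compensation data already precede the 12- and 24-month outcomes. A claim first recorded at 6 months may also date from the first weeks.

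Much of this stands:
- A reader might infer that the study will mistake consequences of poor health for effects of compensation. The documents do not support that. They speak of associations and predictors, the policy wording is a hope, and the analysis could still be ordered properly.
- Not every item is open to reversal. Previous claim history predates the crash, and actual fault, unlike reported blame, is fixed at the crash. Participants found through the regulator's databases have some claim information at recruitment, but they are only part of the cohort.
- The size is assumed. If only baseline health drives claiming, baseline adjustment is enough and the bias is zero.

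What does not answer the point is the stated adjustment. Taken at baseline, it leaves health change up to the interview uncontrolled. Taken at the same visit, adjusting for disability conditions on a primary outcome. Nor can later analysis wording give the 6-month outcome an earlier compensation record in Table 2.

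**Conclusion.** The point holds as a cheap improvement. For claim made, legal representation, disputes, medico-legal assessments, costs and satisfaction, the model as described cannot separate prediction of poor outcome from its consequence. Previous claim history and actual fault are outside the point.

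Under the assumed inputs, the false same-visit effect after baseline adjustment is about 0.1 to 0.4 SD if health after baseline drives the exposure, and none if only baseline health does. The article gives no figure that would place the study within that range.

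A reader might also conclude that the lagged model should replace the same-visit model as the sole primary analysis. That goes too far, because the lagged model removes real effects already present at the earlier visit. The simulations contain no unmeasured confounding. They show that this one bias can be removed, not that the lagged estimate is causal.

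**What to change.** For objective 2, add a lagged analysis: compensation status known at one visit predicts the outcome at the next (6 to 12 months, 12 to 24 months), adjusted for baseline and for the value of that outcome at the earlier visit. Report it beside the same-visit mixed model. State that any directional or policy statement rests on the lagged result. Label same-visit associations as non-directional, including all those at 6 months and those for claims cost. Say at which visit the disability and pain adjustments are taken.

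The planned interviews already supply the data, so the cost is analysis wording. The lagged estimate omits effects realised by the earlier visit, gives nothing for 6-month outcomes, and keeps some residual bias if the health scores contain measurement error. It should be read alongside the same-visit model and not replace it.

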### Baseline and follow-up data and study endpoints

Data from multiple domains will be recorded at baseline and the follow-up interviews as reported in Table 
2. Standardised instruments are used that assess the relevant domains based on previous research.

The primary outcomes are health related quality of life, disability and functioning at 6, 12 and 24 months after injury in motor vehicle crash. The secondary outcomes are pain status, psychological health, return and modification to work status, social outcomes, role of compensation and health care utilisation.

### Data linkage

Pre-injury health status is recognised as a confounder in studies of health outcomes after motor vehicle crashes. It can be measured by recall from the injured person but this may be biased. To avoid this, participant consent will be obtained to access Medicare records for the 12 month period prior to the crash date and for two years after the crash. These data will be linked with the data collected directly from participants. The details of variables that will be collected from Medicare records are listed in Table 
3. Previously a systematic review has reported consent rate to range between 39%-97% for data linkage
[20]. It was observed that in general, individuals tend to consent to the use of their data for record linkage, with exceptions in specific populations or minorities. We anticipate a consent rate of approximately 80% for the study.

**Table 3 T3:** Data collected through Medicare and Pharmaceutical Benefit scheme

**Variables from medicare data**	**Description**
Date of service	Date on which the provider performed the service
Date of processing	Date on which Medicare processed the payment of a claim for the service
Medicare benefits Item description	Describes the service provided by the provider as per Medicare Benefits Schedule
Medicare item number	A number that identifies the service provided by the provider as per Medicare Benefits Schedule
Provider charge	The amount the provider charged for the service
Schedule fee	The fee listed in the Medicare Benefits Schedule
Benefit paid	The Medicare benefit paid to the claimant
Patient out of pocket	The amount the patient is out of pocket i.e. provider charge minus benefit paid Bill
Type	Method by which the Medicare benefit was claimed i.e. cash, bulk bill, cheque to claimant, cheque to provider via claimant, PCE (Easy claim patient claim), simplified bill and EFT
Scrambled ordering provider number	A scrambled provider number identifying the doctor who referred the service scrambled
Rendering provider number	A scrambled provider number identifying the doctor who provided the service
Date of referral	The date of referral or request for a service by a provider
Rendering provider postcode	Postcode of servicing provider’s practice location
Ordering provider postcode	Postcode of referring provider's practice location
Hospital indicator	An indicator of whether the service was performed in hospital
Provider speciality	Speciality of the provider as at time of service
Item category	From the hierarchical system of the Medicare Benefits Schedule
**Variables from Pharmaceutical Benefits Scheme (PBS) claims data**	
Date of supply	The date on which the PBS item was supplied
Date of prescribing	The date on which the prescription was written PBS
Item code	Number which indicates item prescribed as per Schedule of
Pharmaceutical benefits item description	Item name description as it appears in the Schedule of PBS
Pharmaceutical benefits patient category	Refers to the patient's concessional status at the time of supply of the benefit of the item
Patient contribution	The contribution actually paid by the patient
Net benefit	Benefit that Medicare paid to the Pharmacy
Scrambled prescriber number	A scrambled prescriber number identifying the doctor who prescribed the PBS item
Pharmacy postcode	Postcode of Pharmacy where the prescription was dispensed
Form category	Description of script type, e.g. OR: Original, RE: Repeat, DS, Deferred Script, AU: Authority, AR: Authority Repeat
Code	Code allocated by the WHO Collaborating Centre for Drug Statistics
ATC name	According to the Anatomical Therapeutic Chemical (ATC) classification system
Prescriber derived major speciality	Speciality of prescribing doctor

### Study size

Allowing for 30% loss to follow-up a total of 2400 participants will be recruited at baseline. It is anticipated that a sample size of 1,500 is required at 24 months follow-up for linear and logistic regression statistical analyses. Allowing for a 25-30% refusal rate, nearly 3200 participants will be screened for the study. The sample size calculations are for 90% power, to detect independent effects of about 5% of the size of the variable in multiple linear regression analysis. These calculations are based on experience from the pilot study
[31].

### Data protection

All screening data will be entered on a secure platform, the Research Electronic Data Capture (REDCap) which is maintained by the Information and Communication Department, University of Sydney. Additionally, data from REDCap will be stored on a password protected Excel database which will be secured on an additional password protected USB stick stored in a lockable cabinet. Cloudstor, a secure large file transfer system will be used for Internet data transfer among the research teams at University of Sydney and University of Queensland.

For Medicare and Pharmaceutical Benefit Scheme data linkage, four researchers of the team have been given access to the data. A protocol developed by the Australian Institute for Health and Welfare, for linking two or more data sets held by the institute will be complied with, for data linkage
[31].

### Bias

We aim to minimise sampling bias by enrolling an inception cohort within 28 days of the crash event. Recruitment of participants from a range of different sources will result in a heterogeneous cohort of people injured in road crashes, including a range of injury severity. Participants will be broadly representative of the injured population of NSW in terms of injury severity and type, and demographic details. Recruitment utilising data police crash reports will allow recruitment of people injured in road crashes from rural and remote areas of NSW.

Measurement bias will be minimised by using pooled and de-identified data analysed by study investigators and staff who have not participated in recruitment or follow-up of individual participants. The study uses measurement scales and outcome instruments that have been previously shown to be valid and reliable, reducing measurement bias in the study. Interviews are conducted by trained staff using CADI.

Bias due to selective loss to follow-up will be minimised by using strategies such as, flexible time for calling, computer aided telephone interviews, engaging with participants via regular newsletters, and by recording multiple telephone numbers for contact so as to ensure high follow-up rates. Loss to follow up interview at any time point will not preclude an attempt to follow-up for subsequent interview. The Prospective Outcomes of Injury Study (POIS) study from New Zealand has reported 38% of those who did not participate at 12 months follow up interview participated at 24 months
[32].

In the analysis phase, appropriate strategies will be used to assess potential confounding factors. While every attempt will be made to ensure complete data collection for all study participants, missing data are inevitable. If need be, the use of multiple imputation methods for missing data will be used to maximise available data. In multiple imputations, missing values for any variable are predicted using existing values from other variables. Multiple imputation accounts for missing data by restoring not only the natural variability in the missing data, but also by incorporating the uncertainty caused by estimating missing data
[33]. The performance of multiple imputation in a variety of missing data situations has been well-studied and it has been shown to perform favourably
[34,35].

### Data analysis

Summary statistics will be used to describe the profile of participants in the study at each time point. Frequencies and percentages, means and standard deviations, and medians and interquartile ranges, will be used to summarise key predictors and outcomes, depending on the distribution of the data collected for these variables. Key participant groups (for example, participants lost to follow-up vs. not lost to follow-up, compensable vs. non-compensable) will be compared using chi-square tests for categorical characteristics, and either independent t-tests or Mann–Whitney U-tests for continuous variables depending on the distributional characteristics of particular variables.

To analyse change in outcome over time, and to explore predictors of outcome, multilevel mixed effects regression models will be fitted with a random effect for patient to allow for excess correlation in outcomes measured repeatedly from the same participant. Mixed effects modelling is warranted due to the longitudinal nature of the study. Logistic regression will be used for binary outcomes and linear regression for continuous outcomes. Univariate and bivariate models will be performed to explore the association between individual predictors and each outcome. To establish whether the rate of change in the outcome differs across participant sub-groups (for example, compensable vs. non-compensable), an interaction term between each variable and follow up time point will be included in the regression model. Interaction terms between various predictors will be examined in order to identify potential effect modification. Multivariate mixed effects models will be used to identify important predictors of outcome, adjusted for potential confounders, and including key a priori interactions. Odds ratios, adjusted odds ratios, and 95% confidence intervals will be reported for logistic models, while coefficients and 95% confidence intervals will be reported for linear models.

